#### 9.1.2 DEFINITION OF CRITICAL ADVERSE EVENTS

Critical adverse events in this trial are IUFD, sepsis, ICU admission, multiple organ failure, artificial ventilation, and total hysterectomy in subjects (mother, fetus).

#### 9.1.3 DEFINITION OF SERIOUS ADVERSE EVENTS

If CI or SIs determine that an adverse event meets the following five criteria (1. to 5.), it is considered a serious adverse event:

1. Death or risk of death
2. Those that require hospitalization at a medical institution or extension of the hospitalization period for treatment
3. Disability or risk of disability
4. Serious according to 1-3
5. Congenital diseases or abnormalities in later generations

Hospitalization scheduled before participation in the trial, hospitalization for laboratory purposes, or extension of the hospitalization period is not considered a serious adverse event. If IUFD or child death occurs, it is determined as 1.

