### 9.1 DEFINITION

#### 9.1.1 DEFINITION OF ADVERSE EVENTS

Adverse events in this study are defined as clinically problematic events among all unfavorable symptoms, signs, illnesses, and laboratory abnormalities that occur in subjects (mother, fetus) from the start of protocol treatment to the termination of pregnancy (or when study participation has discontinued). It does not matter if it has a causal relationship with protocol treatment. In infants, they are defined as clinically problematic events among all unfavorable symptoms, signs, illnesses, or abnormal laboratory abnormalities that occur between postpartum and the end of observation. However, IVH, PVL, RDS, meconium aspiration syndrome (MAS), TTN, PPHN, sepsis, NEC, which are defined as neonatal complications in this trial, localized intestinal perforation, and symptomatic PDA are not reported as adverse events in infants; but they are reported as serious adverse events if they fall under the definition of serious adverse events.

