|   |                                                                                                                                                                                                                        | Absent              | -                 | -                                                       | -                                                   |
| 2 | 2 Hospitalization or extension of the hospitalization period for treatment
3 Disability or risk of disability
4 Death or serious according to 1-3
5 Congenital diseases or abnormalities in later generations | Present             | Possible          | 15 days                                                 | 15 days                                             |
|   |                                                                                                                                                                                                                        |                     | Not possible      | -                                                       | -                                                   |
|   |                                                                                                                                                                                                                        | Absent              | -                 | -                                                       | -                                                   |

When reporting to the Jichi Medical University Central Clinical Research Ethics Committee, Unified Form 8 should be used and prepared by PI with the cooperation of CI or SI from other institutions. In addition, each time PI prepares Unified Form 8, the report should be sent to CI of all medical institutions to share information, and measures such as alerting should be taken as necessary. Furthermore, each CI, including PI, reports the information on the outbreak of “disease, etc.” to the director of each implementing medical institute, and takes preventive measures and countermeasures against the outbreak of “disease, etc.”, with the cooperation of the director of the implementing medical institution as necessary.

To report to the Minister of Health, Labour and Welfare, in principle, use the Disease Reporting System (<https://mh.cr-adr.com/adr/v1/>) to prepare Appendix Form 2-1 and send it to the Pharmaceuticals and Medical Devices Agency ( ).

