| D. Safety evaluation items for infants                                                                                                                                                         |                                   |                                                                                                                                                                                                                                                                                                                                                    |
| Incidence rates of serious adverse events                                                                                                                                                      | Safety analysis target population | (1) We will perform coding of events using MedDRA, and count the numbers according to SOC and PT. (2) The numbers, frequencies, and 95% CI.                                                                                                                                                                                                        |
| E. Other evaluation items in the current trial                                                                                                                                                 |                                   |                                                                                                                                                                                                                                                                                                                                                    |
| Vital signs (body temperature, pulse, blood pressure)                                                                                                                                          | Mainly FAS, followed by PPS.      | (1) Summary statistics*, at each observation point, (2) box-plots                                                                                                                                                                                                                                                                                  |

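### Section 9.1.3 counts a hospital stay extended for treatment as serious and then excludes extended stays without qualification, so infant serious adverse events have no single definition

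*Protocol*

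**What the plan says.** Section 9.1.3 lists five grounds on which an adverse event is serious. The second is: "Those that require hospitalization at a medical institution or extension of the hospitalization period for treatment". The first, "Death or risk of death", and the third, "Disability or risk of disability", cover risk as well as outcome. The section then closes with the exception: "Hospitalization scheduled before participation in the trial, hospitalization for laboratory purposes, or extension of the hospitalization period is not considered a serious adverse event".

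The reporting table in section 9.6.2, which sets deadlines for events judged related to the study, lists among its serious categories: "Hospitalization or extension of the hospitalization period for treatment".

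Section 9.1.1 names ten neonatal complications (among them respiratory distress syndrome, intraventricular haemorrhage, sepsis and necrotizing enterocolitis) that "are not reported as adverse events in infants; but they are reported as serious adverse events if they fall under the definition". Section 9.6 records only serious events for infants. In section 14.2.4, part D, the single infant safety item is "Incidence rates of serious adverse events".

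On setting, note h to Tables 1.3-2 and 7.5-2 collects infant SAEs from delivery to the infant's discharge. Note g to Tables 1.3-1 and 7.5-1 keeps mothers in hospital from the start of treatment to at least three days after delivery.

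**The concern.** In most trials a loose exception about prolonged stays would matter little, because new admissions would still satisfy the hospitalization ground. Here the infant is an inpatient from the first to the last day of SAE collection. A new admission can hardly occur, so the second ground depends on whether extension counts. Section 9.1.3 answers both yes and no.

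At stake is the infant safety result. Section 2.1.3 says the safety of azithromycin needs detailed study because its dose and duration exceed earlier trials, and that many serious events would prompt consideration of cancelling the trial. Section 9.6.1 requires a report on every SAE whatever its cause. The trial is open-label, with no audit (16.4) and no efficacy and safety committee (16.5). Randomization is stratified by gestational week and type of facility (4.2), not by individual centre, so nothing in the design ensures that sites using one reading contribute equally to both arms.

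For infants the error is also hard to undo. An event outside the listed complications that a site judges non-serious is not recorded as an adverse event at all.

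**Working it through.** **Setting the texts side by side**

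| Place | Extension of stay for treatment |
|---|---|
| 9.1.3, second ground | serious |
| 9.1.3, closing sentence as printed | not serious (no qualifier) |
| 9.6.2 table, second row | serious |

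Two places count it and one excludes it. An event that meets ground 1, 3, 4 or 5 stays serious on either reading, so the conflict concerns events that are serious only because they prolong the stay.

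**How far the rate could move**

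The protocol states no expected infant SAE rate, so there is no figure to reproduce and none can be derived. What follows is an illustration. It assumes that the rates in section 2.1.1 (the series of 55 women) apply, and that seriousness is assigned by type of complication.

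Inputs from 2.1.1: early neonatal death 7%, intraventricular haemorrhage (IVH) 10%, periventricular leukomalacia (PVL) 10%, necrotizing enterocolitis (NEC) 6%, sepsis 4%, respiratory distress syndrome (RDS) 56%, transient tachypnoea (TTN) 42%. Arm size from 5.2.1: 50.

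For a set of complications with rates p, the share of infants with at least one is bounded by:
- lower bound (complete overlap): max(p)
- upper bound (no overlap): min(1, sum of p)
- under independence: 1 − product of (1 − p)

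*Extension never counts.*
- Deaths only: 7%, or 0.07 × 50 = 3.5 infants per arm. This is a floor, because risk of death and risk of disability still qualify.
- Deaths plus IVH, PVL, NEC and sepsis, if these qualify as risk of death or disability: lower 10%; upper 7 + 10 + 10 + 6 + 4 = 37%; independent 1 − 0.93 × 0.90 × 0.90 × 0.94 × 0.96 = 32%. That is 5 to 18.5 infants per arm.

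*Extension for treatment counts.*
- RDS alone, if treated RDS is judged to prolong the stay: 56%, or 28 infants per arm.
- Deaths plus IVH, PVL, NEC, sepsis, RDS and TTN: lower 56%; the sum, 37 + 56 + 42 = 135%, is capped at 100%; independent 1 − 0.680 × 0.44 × 0.58 = 83%, where 0.680 is the product in the previous calculation.

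**What mixing the readings does**

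Suppose a fraction f of infants is at sites that count extension, and take the two lower bounds, 10% and 56%. The pooled rate is 0.56f + 0.10(1 − f): 21.5% at f = 0.25, 33% at f = 0.5 and 44.5% at f = 0.75. The value of f is an assumption and would be unknown in practice. The reported rate would then partly measure which sentence the sites followed.

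**The case against.** The best defence is that the phrase about laboratory purposes was meant to govern both the hospitalization and the extension that follows it. Read that way, only test-related extensions are excluded and the conflict disappears. The 9.6.2 table supports this intention, and section 9 refers to a separate handling procedure, not shown, that may say so. This is plausible, but the printed sentence does not say it, and a site working from 9.1.3 alone can fairly read it the other way.

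The effect is also contained. Events are tabulated by MedDRA class and term, so an unrelated harm has its own row. Most of the listed complications, and bronchopulmonary dysplasia at 28 days (BPD28), are compared by arm in 14.2.3 whatever their seriousness. All maternal adverse events are recorded regardless of seriousness (9.6), and the critical maternal events are defined separately (9.1.2), so a maternal misclassification can in principle be reviewed later. Section 3 also lists side effects for the child. All of this stands and limits the severity. It does not give the infant SAE rate a single meaning.

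A reader might infer that the rate is about 7% on one reading and over 70% on the other. The documents do not support that. The 7% is the early neonatal death rate. A figure above 70% needs BPD28 (72%) to be reported as an SAE, and no section says that it is or is not. Even the 56% depends on a judgement that treated RDS prolongs a stay that prematurity already requires. A reader might also conclude that BPD must join the list in 9.1.1, or that the SAE table must be split. Both are preferences. Making the unlisted events the headline rate would drop serious sepsis, NEC and intestinal perforation from the main safety figure of an antibiotic trial.

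**Conclusion.** The contradiction is real. Section 9.1.3 includes and then excludes the same thing, and 9.6.2 agrees with the inclusion. Because infants are inpatients throughout and only their serious events are recorded, the wording decides whether the second ground applies to them at all. Maternal SAE classification is affected too, with less consequence.

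The size can only be illustrated: about 7% (deaths only) or 10% to 37% (with IVH, PVL, NEC and sepsis) if extension never counts, against 56% or more if it counts and treated RDS is judged to prolong the stay. These ranges rest on a 55-woman series, on seriousness assigned by type of complication and on unknown overlap between complications. They are not expected SAE rates for this trial. They show that the choice of sentence could outweigh ordinary sampling variation: 4 of 50, for example, has an exact 95% interval of 2% to 19%.

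This is a moderate wording error in a safety definition. The primary outcome, its blinded adjudication and its analysis are not affected.

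**What to change.** Reconcile 9.1.3 with 9.6.2. Reword the closing exception so that it covers only a hospitalization, or an extension of one, that was scheduled before participation or is for tests only. It then no longer cancels the second ground. Make sure that the separate handling procedure says the same, and tell all sites which rule applies so that one rule is used throughout.

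If sites have already reported under the present wording, ask each which reading it used and re-check the infant classification against the medical records before the data are fixed.

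The cost is one sentence in the protocol and a note to sites. No new data item or extra table is needed. Sites that have followed the closing sentence literally may report more serious events afterwards.

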#### 9.1.4 DEFINITION OF “DISEASE, ETC.”

Among adverse events, in addition to diseases, disorders, deaths, or infectious diseases, abnormal laboratory test values and various symptom that are suspected to be caused by the implementation of a specific clinical trial are defined as "disease, etc." In addition, that caused by the implementation of clinical study is considered to have a causal relationship with the medicines used in the trial or a causal relationship with the procedure. The causal relationship should be determined by the CI, SI, or PI based on 9.2 Causal Relationship with Study.

### 9.2 CAUSAL RELATIONSHIP WITH STUDY

CI or SI should determine the causal relationship between the trial and all adverse events that occurred in subjects (mother, fetus) and serious adverse events that occurred in infants. Judgment should be made not only due to the time relationship with the start of intervention treatment, but also due to complications, concomitant medications, study procedures, accidents, and other external factors. The causal relationship should be judged and recorded according to the following two criteria (A and B):

A “Causal or undeniable”: judgment is made according to the following a-c, whether known or unknown to occur during the clinical trial or interventional treatment:

- a: Reasonable or possible due to study or interventional treatment.
- b: There is a temporal relationship with the study.
- c: No other cause is shown, and a causal relationship with study cannot be denied.

B “No causal relationship”: judgment is based on the following d-f:

- d: It is not rational to have resulted from study or interventional treatment.
- e: No time relationship is shown.
- f: Other causes are shown.

### 9.3 SEVERITY

CI or SI determines the severity of adverse events that occurred in subjects (mother, fetus) in the following three stages (A to C):

- A “mild”: It is transient, does not impair daily life, and does not require treatment.
- B “moderate”: It causes some problems in daily life and discomfort, and requires treatment.
- C “severe”: It markedly impairs daily life, and treatment such as hospitalization is required.

The CI or SI determines the severity of the adverse event in the child using the Neonatal INC version 1.0 Japanese translation.

### 9.4 PREDICTABILITY

The predictability of adverse events should be determined based on the package insert and interview form. If the nature, severity, or frequency of adverse events does not match, they are considered unknown adverse events.

### 9.5 COLLECTION AND TRACKING PERIOD

CI or SI should collect and record adverse events starting from the treatment start date. Clinical findings present on the date of consent are considered complications and not adverse events. However, exacerbations of complications are recorded as adverse events. As a rule, “disease etc.” and serious adverse events that are determined to have a causal relationship with the trial should be followed up to recovery or improvement as much as possible. Follow-up should be terminated when CI determines that further recovery is difficult or unfollowable due to death, disability, sequelae, etc. Non-serious adverse events that are not causally related to the trial are not specifically followed up in the trial, regardless of the outcome.

Regardless of the severity of adverse events, any adverse events that occur should be collected and recorded until the end of each subject's participation in the trial.

## 9.6 ADVERSE EVENT REPORTS

For all adverse events occurring in subjects (mother, fetus), the event name (diagnosis name), onset date, severity, causality, predictability, outcome, and outcome judgment date are investigated, and are entered in eCRF. For infants, only for serious adverse events, the event name (diagnosis name), onset date, severity, seriousness, causality, predictability, outcome (recovery, remission, unrecovered, sequelae, death, unknown), and outcome judgment date are investigated, and are entered in eCRF. Of all adverse events occurring in subjects (mother, fetus) and children, “disease, etc.” should be reported based on 9.6.2 Reporting of Diseases, etc., and serious adverse events should be reported based on 9.6.1 Reporting of Serious Adverse Events.

### 9.6.1 SERIOUS ADVERSE EVENT REPORTS

If serious adverse events occur in subjects (mother, fetus) or infants, SI who has obtained the information should promptly report it to CI. CI should promptly grasp the seriousness of adverse events and response status, and should consider necessary responses (and treatments). CI should prepare a contact form according to “Pharmaceutical Disease Report (Unified Form 8)” for serious adverse events regardless of whether there is a causal relationship, and should report it to PI and the study secretariat by e-mail. PI and the study secretariat should convey information to CIs of other medical institutions. If a causal relationship cannot be denied, in addition to the procedures in this section, a report will be made based on 9.6.2 Reporting of “Disease, etc.” In addition, CI should adopt necessary measures such as reporting to the director of the implementing medical institution in accordance with the rules and procedure manual of the implementing medical institution.

PI e-mail: [contact]

Study Secretariat e-mail: [contact]

### 9.6.2 REPORTING OF “DISEASE, ETC.”

If a serious “disease, etc.” (a serious adverse event for which a causal relationship cannot be ruled out) occurs, the SI who has knowledge of the event will report it to the CI at his/her institution. Upon receiving the report, the CI will report it to the administrator of the medical institution at that institution and notify the PI and the study office. Thereafter, depending on the predictive nature of the “disease, etc.”, PI must report to the Jichi Medical University Central Clinical Research Ethics Committee and the Minister of Health, Labour and Welfare by the reporting deadline.

Submission deadline for unapproved/off-label use

|   | Type of adverse events                                                                                                                                                                                                 | Causal relationship | Predictive nature | Deadline for Central Clinical Research Ethics Committee | Deadline for Minister of Health, Labour and Welfare |
|---|------------------------------------------------------------------------------------------------------------------------------------------------------------------------------------------------------------------------|---------------------|-------------------|---------------------------------------------------------|-----------------------------------------------------|
| 1 | 1 Death or risk of death                                                                                                                                                                                               | Present             | Possible          | 7 days                                                  | 7 days                                              |
|   |                                                                                                                                                                                                                        |                     | Not possible      | 15 days                                                 | -                                                   |
|   |                                                                                                                                                                                                                        | Absent              | -                 | -                                                       | -                                                   |
| 2 | 2 Hospitalization or extension of the hospitalization period for treatment
3 Disability or risk of disability
4 Death or serious according to 1-3
5 Congenital diseases or abnormalities in later generations | Present             | Possible          | 15 days                                                 | 15 days                                             |
|   |                                                                                                                                                                                                                        |                     | Not possible      | -                                                       | -                                                   |
|   |                                                                                                                                                                                                                        | Absent              | -                 | -                                                       | -                                                   |

When reporting to the Jichi Medical University Central Clinical Research Ethics Committee, Unified Form 8 should be used and prepared by PI with the cooperation of CI or SI from other institutions. In addition, each time PI prepares Unified Form 8, the report should be sent to CI of all medical institutions to share information, and measures such as alerting should be taken as necessary. Furthermore, each CI, including PI, reports the information on the outbreak of “disease, etc.” to the director of each implementing medical institute, and takes preventive measures and countermeasures against the outbreak of “disease, etc.”, with the cooperation of the director of the implementing medical institution as necessary.

To report to the Minister of Health, Labour and Welfare, in principle, use the Disease Reporting System (<https://mh.cr-adr.com/adr/v1/>) to prepare Appendix Form 2-1 and send it to the Pharmaceuticals and Medical Devices Agency ( ).

Regarding all “disease, etc.” that have occurred in the trial, the status of outbreaks of “disease, etc.” should be reported to the Jichi Medical University Central Clinical Research Ethics Committee and directors of the implementing medical institutions in the annual report.

